## Abstract

**Background:**

Due to the growing gap between the demand and supply of therapeutic services for people suffering from depression, with this study, we are investigating the effectiveness and factors of influence of new approaches in group treatments for depression. Two previous studies have already identified bouldering psychotherapy (BPT) as an effective option. It combines psychotherapeutic interventions with action- and body-oriented bouldering exercises. Mental model therapy (MMT) is a new cognitive-behavioral approach for treating depression. It focuses on identifying cognitive distortions, biases in decision making, and false assumptions and aims to correct and replace them with useful mental models. We aim to investigate the effectiveness of the interventions compared with a control group (CG) and to assess the factors of influence in a mixed methods approach.

**Methods:**

The study is being conducted as a randomized controlled intervention trial. Adult participants with unipolar depression are being randomized into three groups (BPT, MMT, or CG), and the first two groups are undergoing a 10-week treatment phase. CG follows their individual standard treatment as usual. A priori power analysis revealed that about 120 people should be included to capture a moderate effect. The primary outcome of the study is depression rated with the Montgomery and Asberg Depression Rating Scale (MADRS) before (t0), directly after (t1), and 12 months after the intervention phase (t2). Data are being collected via questionnaires, computer-assisted video interviews, and physical examinations. The primary hypotheses will be statistically analyzed by mixed model ANOVAs to compare the three groups over time. For secondary outcomes, further multivariate methods (e.g., mixed model ANOVAs and regression analyses) will be conducted. Qualitative data will be evaluated on the basis of the qualitative thematic analysis.

**Discussion:**

This study is investigating psychological and physical effects of BPT and MMT and its factors of influence on outpatients suffering from depression compared with a CG in a highly naturalistic design. The study could therefore provide insight into the modes of action of group therapy for depression and help to establish new short-term group treatments. Methodological limitations of the study might be the clinical heterogeneity of the sample and confounding effects due to simultaneous individual psychotherapy.

**Trial registration:**

ISRCTN, ISRCTN12347878. Registered 28 March 2022, 
https://www.isrctn.com/ISRCTN12347878.

**Supplementary Information:**

The online version contains supplementary material available at 10.1186/s13063-023-07629-x.

## Background

Depression is one of the most common mental illnesses in the world [1] and will be the most frequent health impairment by 2030 according to estimations of the World Health Organization (WHO) [2–4]. At 11.6%, the current lifetime prevalence in Germany is similar to other industrialized nations [5]. Following clinical guidelines, medication and psychotherapy are the most commonly recommended treatments for depression [6, 7]. In an outpatient care setting, psychotherapy—individual or group—is effective with moderate effect sizes [8] and almost all psychotherapies are equivalently effective [9], so patient preference plays an important role in the choice of therapy. On the other hand, more than half of the patients who receive therapy do not respond, and only one third recover [10]. During the COVID-19-crisis, the need for psychotherapeutic treatment has risen enormously due to higher prevalence rates of depression and anxiety [11]. Effective and attractive group programs might be able to respond to the lack of therapeutic resources [12], but to date, they are underrepresented in the outpatient care setting and in research [13]. They should be as effective as existing treatment options, available to more individuals, attractive, and easy to access.

To address the growing demand for treatment options, we developed two new short-term group therapies for outpatients suffering from depression: bouldering psychotherapy (BPT) and mental model therapy (MMT).

BPT is an approach that combines psychotherapeutic elements and topics (e.g., mindfulness and self-efficacy) with bouldering exercises. In recent years, therapeutic climbing, especially rock climbing and bouldering (climbing without rope in moderate heights), has moved into the focus of scientific research concerning mental health [14], resulting in several studies that have indicated positive effects of climbing and bouldering on a variety of illnesses, such as anxiety [15–17], depression [15, 18], eating disorders, post-traumatic stress disorder [16, 17], and attention deficit hyperactivity disorder [19, 20]. Such effects might be moderated by an increase in cognitive functioning [18], self-confidence, self-esteem, and self-efficacy [21], as well as affective responses [22] and social skills [18]. Up to now, there have been two randomized, controlled trials investigating the effects of a psychotherapeutic bouldering intervention, called BPT, on depressive symptoms. It was shown that BPT was superior to an active control group (CG) [23, 24] as well as to a waitlist CG directly after the end of the treatment phase [25, 26] and in the long term [27, 28]. Furthermore, BPT was not inferior to a group cognitive behavioral therapy (CBT) in its effectiveness as an intervention for depression [28] and proved to be cost-effective [29].

Mental model therapy (MMT) is based on a cognitive approach. Mental models are seen as universal rules that are applicable to private and professional life, screening for relevant information and reducing the flood of incoming information to a reasonable amount that can be processed. In contrast to CBT, which focuses on the acute emotional effects of dysfunctional thinking, MMT is based on the assumption that cognitive distortions, biases, and false assumptions have a negative influence on executive cognitive functions, such as foresight, goals, priorities, decision-making, postponing rewards, and mental flexibility in the presence of situational changes [30, 31]. Failures in such areas can result in stress, low self-esteem, and even in low social status. In a comparative analysis of different psychotherapies for depression, the good efficacy of Self-Examination Therapy stood out [32]. This therapy conveys a simple model: the resolution of changeable problems and the acceptance of the unchangeable [33]. Thus, even a single mental model can have a particularly good antidepressant effect. In MMT, we pursue the teaching of different mental models with memorable terms for cognitive distortions, thus expanding the participants’ language and conception of the world. The sources of these models lie in humanistic psychology, behavioral economics, stoic philosophy, and CBT. MMT is intended to help people develop healthy and self-actualizing personalities and thus references humanistic psychotherapy. It helps identify systematic cognitive distortions and biased decision making by using insights from behavioral economics [34]. With its acceptance of the unchangeable, MMT is in the tradition of stoic philosophy and will eventually help overcome the intention-behavior gap through the development of habits based on CBT.

In summary, MMT has been designed to have a beneficial effect in the treatment of stressful life situations and mental disorders, such as burnout and depression.

The goal of this study is threefold. First, we will compare both interventions with a naturalistic control group to test the hypothesis that individuals in the intervention groups (IGs) will experience a significantly greater reduction in their depressive symptoms than individuals in the control group (CG). CG is allowed to follow their individual prescribed treatment plans (treatment as usual) with no study-specific offer during the intervention period.

Second, we will analyze a wide range of potential mediating and moderating factors, such as anxiety [24], self-efficacy [35], mindfulness, treatment preference, and physiological factors. Moreover, we will assess blood biomarkers in an exploratory approach: Osteocalcin is a hormone produced by osteoblasts in the bone system. Besides its role in bone mineralization, it serves as a bone-brain signal. It can cross the blood-brain barrier and activate specific receptors in the brain [36, 37]. Animal studies on depression have shown sex-dependent antidepressant and anxiolytic effects of osteocalcin [38, 39]. Osteocalcin activity may be driven by physical activity in humans [40]. Furthermore, lipids, including cholesterol and low-/high-density lipoprotein, are altered in depression [41] and are influenced by patients’ physical activity [42]. Levels of sphingolipids (e.g., ceramide [43]) and corresponding enzyme activities (e.g., acid sphingomyelinase [44]) or their splice variant composition [45] are associated with major depressive disorder. Thus, serum lipid levels and the expression or activities of enzymes of the sphingolipid metabolism, including acid sphingomyelinase and sphingomyelin synthase catalyzing the reverse reaction [44], could be expected to change or normalize during BPT and MMT. These changes could be similar to the changes that occur during pharmacological antidepressant treatment [46]. Moreover, current pathomechanisms of depression include disturbances of the hypothalamic-pituitary-adrenal axis (e.g., glucocorticoid receptor sensitivity [47]), neurotrophic homeostasis (e.g., brain-derived neurotrophic factor (BDNF) levels [48]), and inflammatory processes (e.g., migration inhibitory factor (MIF) [49]). The effectiveness of BPT, MMT, or both might therefore also be reflected in the restoration of such stress regulators, growth factors, and inflammatory markers. The spectrum of biomarkers will be extended according to new literature and the detection and establishment of new assays.

In addition to the quantitative analysis, qualitative semi-structured interviews will be conducted to investigate additional specific modes of action and factors of influence.

## Methods

### Aims and hypothesis

The aim of the current study is to examine whether (a) BPT and (b) MMT are more effective in reducing participants’ depressive symptoms compared to a control group receiving treatment as usual. Therefore, we are comparing both IGs with a CG in a randomized and controlled but yet naturalistic design.

#### Research hypothesis

I.Patients in the bouldering psychotherapy (BPT) improve significantly more than patients in the control group (CG) regarding the severity of depression.II.Patients in the mental model therapy (MMT) improve significantly more than patients in the control group (CG) regarding the severity of depression.

Effects on secondary outcomes (e.g., anxiety, self-efficacy) will be analyzed in an exploratory fashion. Regarding the biomarkers, it is expected that participation in the BPT will lead to a greater increase in blood osteocalcin and brain-derived neurotrophic factor levels than in the MMT and CG. We expect higher serum acid sphingomyelinase activities to correlate with greater improvement in depression severity in both treatment groups. Additional sphingolipid parameters, growth factors, and inflammatory markers will be analyzed and are expected to normalize in both IGs. Whereas these assumptions were based on previous studies, sample size estimation was based solely on the number of participants required for the psychotherapeutic effect and not adjusted any further.

Qualitative data will be used to explore the extent to which participants perceive the interventions to be helpful, which components or factors of influence they feel are most important, and which limitations or barriers they perceive. In line with Grawe [50], the results of the qualitative analysis will be used to further develop hypotheses on potential factors of influence with respect to BPT and MMT.

In this article, we describe the study protocol for *new ways to cope with depression*. This protocol will serve as a reference for the forthcoming papers that will report the results of the study.

### Study design and setting

The study was designed as a randomized, controlled, interventional, prospective, longitudinal, assessor-blinded study with three arms (BPT, MMT, CG). The overall start date was on October 1, 2021. Recruitment began on March 29, 2022, and will continue through February 28, 2023, in the Erlangen/Nuremberg/Fuerth region, a metropolitan region of three cities. After passing a diagnostic screening interview, participants are randomly assigned to one of the IGs (BPT or MMT) or the CG. Both IGs consist of 10 weekly 2-h sessions with a maximum of 11 participants and are each led by two therapists. After the end of the intervention phase, participants in the CG will be offered preferential admission to an outpatient BPT group at University Hospital Erlangen. MMT will be directly evaluated in an RCT design because many of its single components are well-established and well-investigated cognitive distortions. As it is very unlikely that the novel long-term focus on transforming thinking errors into appropriate goal-oriented thinking and action could lead to significant side effects, a previous open trial was not deemed mandatory. In all four consecutive waves of the study, the interventions are taking place simultaneously. To collect the data, structured video interviews are being conducted at baseline before the onset of therapy (t0), after the intervention (t1), and 12 months after the end of the intervention (t2). In addition to the interviews, participants are required to complete a series of questionnaires online (at t0, t1, and t2) and to undergo a physical examination with blood sampling (at t0 and t1 at about the same time of day). All procedures were approved by the Friedrich-Alexander-Universität Erlangen-Nürnberg Ethics Committee (Ref. 21-332-B) on December 13, 2021. The SPIRIT participant timeline is shown in Fig. 1, and the SPIRIT checklist is provided as an Additional file [51]. Trial Registration Data are presented in Table 1 (ISRCTN12347878, Registration date: March 28, 2022, registered prospectively).

**Fig. 1 Fig1:**
[figure not shown]
SPIRIT figure. Participant timeline. Superscript digit one (^1^) indicates the following: only participants in the intervention groups. BMI, body mass index; BPT, bouldering psychotherapy; BSA-F, Bewegungs- und Sportaktivität Fragebogen; CG, control group; CRT-3, Cognitive Reflection Test; FEPiG, Fragebogen zum Erleben von therapeutischen Prozessen in der Gruppe; GAD-7, Generalized Anxiety Disorder—Scale-7; IE-4, Internal External Locus of Control; MADRS, Montgomery and Asberg Depression Rating Scale; MMT, mental model therapy; MSMQ, Multidimensional State Mindfulness Questionnaire; SMS-PA-12, State Mindfulness Scale for Physical Activity; SOC, Sense of Coherence Scale; SWE, Skala zur Allgemeinen Selbstwirksamkeit

**Table 1 Tab1:** Trial registration data

**Data category**	**Information**
1. Primary registry and trial identification number’	ISRCTN 12347878
2. Date of registration in primary registry	March 28, 2022
3. Secondary identifying numbers	-
4. Source(s) of monetary or material support	University Hospital Erlangen
5. Primary sponsor	University Hospital Erlangen
6. Secondary sponsor(s)	-
7. Contact for public queries	see Point 8
8. Contact for scientific queries	PD [name], [contact]
9. Public title	New ways to cope with depression
10. Scientific title	New ways to cope with depression—study protocol for a randomized controlled mixed methods trial of bouldering psychotherapy (BPT) and mental model therapy (MMT)
11. Countries of recruitment	Germany
12. Health condition(s) or problem(s) studied	Depression
13. Intervention(s)	Intervention group receiving the bouldering psychotherapy (BPT)
	Intervention group receiving the mental model therapy (MMT)
	Control group (CG)
14. Key inclusion and exclusion criteria	Inclusion criteria: 1. Depressive episode, assessed via virtual diagnostic screening interview based on the DSM-V diagnostic criteria 2. Informed consent to participate in the study (especially regarding the randomized allocation, anonymous storage of data, and data collection) 3. Ability and availability to come to the therapy locations and time to participate as well as access to digital applications for video or telephone interviews
	Exclusion criteria: 1. Age < 18 years 2. Presence of current severe mental illnesses that complicate participation in group therapy (e.g., psychosis, mania, current self-injury, acute substance dependence, current suicidality) 3. Physical contraindication for climbing (physical ailments or pregnancy) 4. Body Mass Index (BMI) < 17.5 or > 40 5. Current treatment confounded with study outcomes (participation in psychotherapeutic group therapy, initiation/change in psychotropic medication within 8 weeks prior to the intervention)
15. Study type	Randomized controlled prospective assessor-blinded longitudinal clinical intervention study
16. Date of first enrollment	Began on March 29, 2022
17. Target sample size	120
18. Recruitment status	Ongoing
19. Primary outcome(s)	Depression measured with the Montgomery Asberg Rating Scale (MADRS) score from a third-party assessment in computer-assisted video interviews
20. Key secondary outcomes	Anxiety, self-efficacy, sense of coherence, locus of control, (mind- and body-based) state mindfulness, physical activity, mechanisms of therapeutic change in group therapy, blood concentration of osteocalcin, sphingolipid parameters, growth factors and inflammatory markers, qualitative factors of influence
BPT specific	Hand strength, core stability, BMI, body fat percentage, muscle percentage
MMT specific	Cognitive processing

### Sample size estimation

ITT sample size was calculated on the basis of the authors’ previous experiences with BPT. Both studies on the effectiveness of BPT showed a moderate effect size (Cohen’s *d*s of 0.55 to 0.77) on depression severity [24, 25]. On the basis of effect sizes for CBT [9], comparable effect sizes are expected for MMT. Thus, an a priori power analysis to identify a moderate effect of *f* ≥ 0.295 was computed with the statistical program *G*Power* version 3.1.9.7. The calculations for the mixed ANOVA with two repeated measures as within-subjects factors and three groups as between-subjects factors and a group × time interaction revealed a total sample size of 114 participants. Power was set at 80%, *α* = .05, a correlation between repeated measurements of .50, and a nonsphericity correction of 1. To create three equal-sized groups each consisting of 10 participants across the four waves of recruitment, we planned to recruit a total of 120 participants, resulting in a total of 40 participants per group.

### Recruitment strategies

We are using several recruitment strategies to ensure the highest possible representativity of the sample: Informational materials (e.g., flyers, posters) are being distributed throughout the Erlangen/Nuremberg/Fuerth region at psychiatric hospitals, psychotherapist offices, primary care physician offices, pharmacies, health insurance companies, and other psychological and social services (e.g., support groups, counseling centers). Information is also being shared with psychotherapists, psychiatrists, and primary care physicians in outpatient clinics, outpatient training clinics, and private practices, asking them to pass the offer on to patients on their waiting lists. People who have expressed interest in participating and have agreed to be contacted for the upcoming or a later wave of the study are being contacted via email. Before each wave, press releases are being issued and addressed to a variety of local newspapers, and general informative events are being held in auditoriums at the University Hospital Erlangen and online via the platform *Zoom Meetings*. On the Internet, a homepage [52], an Instagram account, and a Facebook account were created and are being updated regularly with the most current information.

### Eligibility of participants

All people interested in participation are invited to attend one of the three general informative events held by the study personnel in each wave. Relevant information about the IGs and an explanation of the participation conditions (e.g., randomization procedure please see “Randomization”) are provided there. Individuals who decide to participate are asked to undergo a computer-assisted diagnostic video screening interview for inclusion and exclusion criteria and to provide written informed consent.

#### Inclusion and exclusion criteria

To increase external validity, only a few inclusion and exclusion criteria are applied. *Inclusion criteria* are fulfilling the diagnostic criteria for an episode of major depression (single or recurrent) according to DSM 5, informed consent to participate in the study (especially regarding randomized allocation and data acquisition), and the ability and time to travel to the therapy locations to participate in the interventions, as well as access to digital applications for video or telephone interviews. The presence (or absence) of depression is assessed by a standardized diagnostic screening interview that is based on the Diagnostic and Statistical Manual of Mental Disorders, Fifth Edition (DSM-V), diagnostic criteria [53]. *Exclusion criteria* are an age younger than 18 years, a body mass index (BMI) under 17.5 or over 40 (for safety reasons in BPT), current participation in another psychotherapeutic group therapy, an initiation of a change or a change in psychiatric medication 8 weeks (or fewer) before the study (starting a medication more than 8 weeks before the study is not a reason for exclusion), a planned inpatient stay during the intervention period, physical contraindication for bouldering (physical ailments or pregnancy), specific severe psychiatric disorders, and acute suicidality. Severe psychiatric disorders leading to exclusion from the study are psychosis within the last 5 years, a manic episode within the last 5 years, substance addiction with substance abuse within the last year, self-harming behavior during the last year, and current organic diseases with symptoms of psychiatric disorders, such as dementia or delirium. For safety reasons, all applicants are screened for suicidality, and only those who are able to comply with a safety plan and are in control of their own safety are included in the study. The safety plan, which is discussed with the applicants, includes information about in-patient crisis intervention at the nearby psychiatric hospital and the 24-h crisis intervention telephone hotline provided by the local mental health services. All inclusion and exclusion criteria are assessed in a diagnostic screening interview by the study personnel.

### Randomization

Blockwise randomization per study wave was performed externally by the Institute of Medical Informatics, Biometry, and Epidemiology (IMBE), Friedrich-Alexander-Universität Erlangen-Nürnberg, only sharing patients’ code, age, sex, and treatment preference. The latter three were used in a stochastic minimization algorithm to reduce group imbalance [54]. More specifically, in each wave, 1000 random permutations of group memberships for the new patients (with equally sized groups) were generated, and the first permutation that minimized the summed chi-square or *F* statistic for group differences with respect to sex, treatment preference, and age was selected; the statistician transmitted the sampled group allocations back to the study center. The randomization algorithm was implemented in the statistical software environment R [55]. After the randomization, participants are informed about their allocation (BPT, MMT, CG) and are given detailed information about their group participation.

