#### Quantitative measurements

The primary hypothesis will be tested via mixed model ANOVAs with which potential interactions between time and group can be detected. To test the first and second hypotheses, a mixed model ANOVA with the between-subjects factor group and the within-subjects factor time as well as the group × time interaction will be calculated. Additionally, multiple regression analyses will be calculated to control for the effects of possible confounding variables (e.g., demographics, additional therapeutic treatments, such as antidepressant medication and psychotherapy).

Secondary outcome variables will be tested in an exploratory fashion with mixed model ANOVAs.

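### The primary mixed ANOVA treats baseline MADRS as a time level and leaves out the factors used in allocation, which gives up precision that an adjusted model would recover at almost no cost

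*Protocol article*

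**What the plan says.** **Allocation (Randomization).** "Blockwise randomization per study wave was performed externally", with equal group sizes in each wave. Of age, sex and treatment preference the section says: "The latter three were used in a stochastic minimization algorithm to reduce group imbalance". Within a wave, 1000 random permutations are drawn and the first one that "minimized the summed chi-square or *F* statistic for group differences with respect to sex, treatment preference, and age was selected". Baseline MADRS is not among the balancing variables.

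**Primary analysis (Quantitative measurements).** Both hypotheses are tested by "a mixed model ANOVA with the between-subjects factor group and the within-subjects factor time as well as the group × time interaction". MADRS is measured at t0, t1 and t2 (Abstract; Study design and setting), so the baseline value enters as a response at one level of the time factor.

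**Covariates (same section).** "Additionally, multiple regression analyses will be calculated to control for the effects of possible confounding variables". The examples given are demographics and concurrent treatment. Baseline MADRS, treatment preference and wave are not named. The Discussion adds that preference is considered at randomization and that preference subgroups can be compared. Neither adjusts the primary test.

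**Planning values (Sample size estimation).** f = 0.295, three groups, two measurements, correlation 0.50, nonsphericity correction 1, α = .05, power 80%, giving 114 patients and 120 planned (40 per arm). The earlier bouldering studies showed d of 0.55 to 0.77.

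**The concern.** Two separate points lie in the same model.

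1. *Baseline as a response.* With t0 and t1 only, the group-by-time interaction is algebraically the comparison of raw changes between arms. A change score subtracts the whole baseline value, although at a correlation of 0.50 only half of it carries over. The surplus is noise. Any chance difference in baseline MADRS also leaks into the estimate through regression to the mean, and MADRS is not one of the balanced variables.

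2. *Balanced factors left out.* Forcing the arms to agree on age, sex, preference and wave reduces the true sampling variability of the arm contrast, to the extent that these factors predict what is analysed. A model that omits them leaves their contribution in the residual and reports a standard error as if allocation had been unrestricted.

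What is at stake is sensitivity. Hypotheses I and II each compare one intervention with control, and at d = 0.55 to 0.59 those contrasts have less than 80% power in the change-score form.

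**Working it through.** **Step 1. Reproduce the plan's figure.** Noncentral F for group × time with 3 groups and 2 measurements: df1 = 2, df2 = N − 3, λ = f²N.
- N = 114: λ = 0.295² × 114 = 9.92, power 0.801. The stated 114 is reproduced.
- N = 120: λ = 10.44, power 0.823.

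This form of λ does not use the correlation, so the stated 0.50 does not itself drive the 114.

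**Step 2. Variance with baseline as a covariate.** Single-occasion variance set to 1, correlation ρ:
- change score: 2(1 − ρ)
- baseline-adjusted: 1 − ρ²
- ratio: (1 + ρ)/2

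| ρ | change | adjusted | ratio | reduction |
|---|---|---|---|---|
| 0.3 (assumed) | 1.40 | 0.91 | 0.65 | 35% |
| 0.5 (plan) | 1.00 | 0.75 | 0.75 | 25% |
| 0.8 (assumed) | 0.40 | 0.36 | 0.90 | 10% |

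The ratio is below 1 for every ρ < 1, so the direction does not depend on the planning value. At ρ = 0.50 the expected change moves by ρ − 1 = −0.5 per unit of baseline. A chance baseline difference of δ between arms therefore shifts the change contrast by −0.5δ; adjustment removes this shift.

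**Step 3. Power for one arm against control.** Two-sided t test, 40 per arm, ρ = 0.50, noncentrality d√(40/2)/√v with v = 1.00 or 0.75. Here d = 0.59 is 2 × 0.295.
- d = 0.55: noncentrality 2.46 → 2.84, power 68% → 80%
- d = 0.59: 2.64 → 3.05, power 74% → 85%
- d = 0.77: 3.44 → 3.98, power 93% → 98%

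**Step 4. Omnibus test.** Rescaled f = 0.295/√0.75 = 0.341, df2 = N − 4.
- N = 120: λ = 13.92, power 92% (82% in Step 1)
- N = 114: power 0.905 (0.801 in Step 1)
- 87 patients in equal groups give 80% power, against 114

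**Step 5. Omitted balancing factors.** The allocation algorithm was simulated under the null: 4 waves of 30, best of 1000 permutations on sex, preference and age, 6000 trials per setting, ρ = 0.50. Assumed: 60% in one sex category, preference split 50/40/10, normal age, equal contributions from the three factors and wave. The share of change variance that they explain is also assumed; the protocol gives none.

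| Factors act on | mean model SE | true SD | SE excess | type I error |
|---|---|---|---|---|
| change, 10% | 0.2355 | 0.2242 | 5% | 0.041 |
| change, 20% | 0.2500 | 0.2265 | 10% | 0.026 |
| level only (all visits equally) | 0.2232 | 0.2259 | none | 0.050 |

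Further simulation runs gave 4–5% at 10% and 9–11% at 20%, with type I error near 4% and 3%. There is a ceiling as a check: if the factors explain 20% and balance is perfect, the excess is 1/√0.8 − 1 = 12%.

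**Step 6. Both changes together.** With baseline and all four factors in the model, the mean SE is 0.1947 at 10% and 0.1945 at 20%, and type I error is 0.053 and 0.048. In the level-only setting, baseline alone as covariate leaves type I error at 0.041; adding the factors brings it to 0.048. The factors should therefore enter together with baseline.

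**The case against.** The strongest reply is that nothing here is invalid. Under randomization the group-by-time test is unbiased for the arm contrast, and the change-score standard error is correct for that estimator. **This stands**: the baseline point is one of efficiency, not error. A reader might infer from it that the reported intervals are wrong, but only the omitted balancing factors could make the standard error overstate the true variability.

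That second effect has a condition. Factors that move MADRS equally at t0 and t1 cancel in a change score, and the simulation then shows no conservatism. The protocol does not say how far age, sex, preference or wave predict change. **This stands too**, so the effect can be stated only conditionally.

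A reader might also infer that the primary test is conservative overall. The documents do not support this. Therapy-group clustering in the intervention arms and single EM imputation can act in the opposite direction.

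Nor is the trial underpowered on its own omnibus calculation, which gives 82% at N = 120. The shortfall concerns the pairwise contrasts at d of 0.55 to 0.59, not at 0.77.

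Finally, the covariate list may be left to an unseen analysis plan, and the additional regressions cover demographics. **This does not stand.** The article names the terms of the primary model and places adjustment outside it.

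**Conclusion.** The point holds as a loss of precision in a stated analysis choice.

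- **Baseline MADRS:** at the plan's ρ = 0.50, adjustment removes a quarter of the variance of the t0–t1 contrast, worth 11 to 12 percentage points of pairwise power at d = 0.55 to 0.59 and about 10 points of omnibus power. The size varies with ρ; the direction does not. These figures concern two occasions, as in the sample size calculation, and not the full three-visit interaction.
- **Balancing factors:** a further overstatement of the standard error, about 4–5% or 9–11% if they explain an assumed 10% or 20% of change variance, with type I error of roughly 4% or 3%; none if they shift all visits equally.

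This describes one feature of the analysis and says nothing about the net error of the final interval. The change should be made, but the existing test is not invalid without it.

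**What to change.** Prespecify the primary model on post-baseline MADRS: either an ANCOVA at the visit of interest or a repeated-measures mixed model for t1 and t2 with arm by visit. Include baseline MADRS, age, sex, treatment preference and wave as fixed covariates. Report the unadjusted group-by-time ANOVA as supportive. Fix the covariate list before outcomes are examined, so that the adjustment cannot look selective.

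The cost is wording. Age, sex and preference are recorded at screening, MADRS at t0, and wave is known by design. The model spends about 8 degrees of freedom: baseline 1, age 1, sex 1, preference 2 (three categories), wave 3. With df2 = 120 − 3 − 8 = 109 and the Step 4 effect size, omnibus power at N = 120 is still 92%.
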